# 1. TRIAL SUMMARY

World Health Organization Registration Data Set

| Title | Index microvascular resistance (IMR)-guided management of heart transplantation |
| --- | --- |
| Primary registry and trial identifying number | ClinicalTrials.gov  NCT 06656065 |
| Secondary identifying numbers |  |
| Sources of monetary or material support | No funding. |
| Primary sponsor | Interventional Cardiology Department Miguel Servet University Hospital. Zaragoza, Spain |
| Secondary sponsors (if any) |  |
| Central contact | [name]  Interventional Cardiology Department Miguel Servet University Hospital. Zaragoza, Spain  [name]  [contact] |
| Study officials/Investigators |  |
| Brief title | IMR-HT study |
| Acronym | IMR-HT study |
| Countries of recruitment | Spain |
| Condition(s) or focus of study |  |
| Interventions |  |
| Key eligibility criteria | Age eligibility: 18 years or older  Sex eligibility: Both  Accepts healthy volunteers: No |
| Study design | Study type: Interventional trial  Allocation: Non-randomized  Intervention model: Single group  Primary purpose: Diagnostic  Phase: N/A |
| Masking | None |
| Date of enrollment | March 25, 2024 |
| Target sample size | 100 |
| Recruitment status | Recruiting |
| Primary outcomes |  |
| Secondary outcomes |  |

# 2. INTRODUCTION

## 2.1. Background and rationale

Acute allograft rejection (AAR) is an important cause of morbi-mortality  after heart transplant (HT), particularly within the first year. Advances in immunosuppression, donor heart evaluation, surgical techniques, and post-transplantation care have led to a gradual reduction in AAR and improved survival after HT over time. Endomyocardial biopsy (EMB) is the gold standard method to guide post-HT treatment, as it represents the best tool to identify rejection in orthotopic HT. However, it is usually repeated up to 5 times during the first year - with some variations depending on each center protocol - and it is potentially associated with serious complications.

Several studies have presented the association between AAR, micro-vasculopathy and cardiac allograft epicardial vasculopathy (CAV).  Index of microcirculatory resistance (IMR) measured early after heart transplantation has been significantly associated with the risk of acute cellular rejection (ACR), and patients with IMR≥15 have higher risk of AAR during 2 years follow-up.

The aim of our study is to evaluate if the use of IMR measured at baseline may be useful in guiding care of patients after HT.

## 2.2. Objectives

| **Primary endpoint** |
| --- |
| Evaluate IMR values and number of EMB performed in the first year after HT. |
| **Secondary endpoints** |
| Analyze the relationship between acute cellular rejection and IMR.  Analyze the relationship between cardiovascular and all-cause mortality and IMR.  Analyze the relationship between graft vasculopathy and IMR.  Analyze the relationship between the variation in the IMR value in the first two months and one year and cardiovascular events.  Analyze the relationship between a combined objective of ACR, heart failure, re-transplantation, cardiovascular mortality, all-cause mortality and IMR.  Assessment of immunosuppressive treatment after the IMR results. |

## 2.3. Trial design

The IMR-HT study is a multicenter, prospective study aimed to guide post-HT management based on IMR. It will enroll consecutive eligible patients who undergo HT in each participation center. Patients undergoing HT will be screened for enrollment. Eligible patients will be informed about the study and will have to provide informed consent prior to being included. The recruitment period of the study is two years.

## 3.2. Eligibility criteria

***Inclusion criteria***

- Heart transplant patients >18 years.
- Patients who have received and signed informed consent.

***Exclusion criteria***

- Patients with hemodynamic instability after HT, including cardiogenic shock or severe coagulopathy.
- Patients with acute cellular rejection before intracoronary physiological assessment.
- Patients with bronchial asthma or bronchopathy with a positive bronchodilation test, which contraindicates the use of adenosine.
- Patients with epicardial coronary lesions with a resting physiological index ≤0.89 or ≤0.80 at hyperemia.
- Patients unlikely to cooperate or with inability or unwillingness to give informed consent.

## 3.3. Interventions

### 3.3.1. Intervention description

Based on IMR results, patient clinical status and the other complementary tests:

- If the IMR is less than 15, the number of biopsies could be reduced or kept the same. No immunosuppressive therapy changes would be made.

- If the IMR is 15 or greater, number of biopsies would be performed as usual per protocol. Immunosuppressive therapy could be intensified or maintained the same.

### 3.3.2. Modifications

N/A

### 3.3.3. Adherence

N/A

### 3.3.4. Concomitant care

N/A

## 3.4. Outcomes

- The **primary outcome** of the study is to evaluate IMR values and number of EMB performed in the first year after HT: Depending on IMR values obtained in the first three months, clinical status and the other complementary tests the physician will be able to modify the number of biopsies established in each center protocol.If the IMR is less than 15, the number of biopsies could be reduced or kept the same. If the IMR is 15 or greater,number of biopsies would be performed as usual per protocol.

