## 5.3. Roles and responsibilities

### 5.3.1. Protocol contributors

**Index of microvascular resistance (IMR)-guided management of heart transplantation**

**IMR-Heart Transplant Study**

**PROTOCOL**

**SUMMARY**

| **Study title** | INDEX OF MICROVASCULAR RESISTANCE-GUIDED MANAGEMENT OF HEART TRANSPLANTATION |
| --- | --- |
| **Short Running Title** | IMR-HEART TRANSPLANT STUDY |
| **Investigators** | [name]  [name]  [name]  [name] |
| **Study aim** | Follow-up assessment of heart transplant patients based on IMR |
| **Hypothesis** | The index of microvascular resistance will serve to reduce the number of endomyocardial biopsies in transplant patients. |
| **Study design** | Multi-center, prospective, observational |
| **Inclusion criteria** | Heart transplant patients >18 years. |
| **Exclusion criteria** | Patients presenting with hemodynamic instability after HT, including cardiogenic shock or severe coagulopathy. Patients with acute cellular rejection before intracoronary physiological assessment. Patients with bronchial asthma or bronchopathy with a positive bronchodilation test, which contraindicates the use of adenosine. Patients with epicardial coronary lesions with a resting physiological index ≤0.89 or ≤0.80 at hyperemia. Patients unlikely to cooperate in the study or with inability or unwillingness to give informed consent. |
| **Primary endpoint** | Number of biopsies performed in the first year.  IMR in transplant patients, in the first three months and one year. |
| **Secondary endpoints** | Cardiovascular mortality and IMR.  Cardiac allograft vasculopathy and IMR.  Acute cellular rejection and IMR.  IMR variation, in the first two months and at one year.  Combined endpoint of ACR, heart failure, re-transplantation, cardiovascular mortality and IMR.  Immunosuppressive therapy and IMR. |
| **Data analysis** | Observational, analytical |
| **Follow-up** | 1 year and annually for five years |

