**HYPOTHESIS**

Number of EMB performed in the first year post-HT could vary depending on IMR values. Low IMR values in the first three months could reduce the number of protocol EMB. Meanwhile, high IMR values would not modify the number of EMB performed, and could even contribute to intensify immunosuppressive therapy.

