***Procedure***

**Invasive physiological evaluation of the coronary microcirculation**

Patients included will undergo a coronary angiography between the first and third month after HT.  This coronary angiography is part of the follow-up protocol in most of the centers. Assessment of IMR, coronary flow reserve (CFR) and fractional flow reserve (FFR) will be performed using the standard technique (9-10,14).

The left anterior descending coronary artery will be evaluated in all patients. Circumflex or right coronary artery could be additionally evaluated at operator’s discretion. An intracoronary pressure and temperature sensor-tipped guidewire (Pressure Wire TM X guide- wire 0.014’, Abbott, IL, USA) will be used to perform the measurements. The tip pressure sensor will be advanced into the mid-to-distal portion of the evaluated vessel. Baseline aortic pressure (Pa) and distal intracoronary pressure (Pd) will be obtained to calculate the resting index Pd/Pa. To measure the mean transit time (Tmn) under basal conditions, intracoronary administration of 3 mL of room-temperature saline will be manually injected three times in succession (3 mL/s). Then maximal hyperemia will be induced using adenosine iv (140 to 180 mg/kg/min) and three additional intracoronary room temperature saline boluses of 3 ml will be administered to determine the mean transit time at hyperemia (Tmnh). Finally, fractional flow reserve (FFR), coronary flow reserve (CFR) and IMR will be calculated using the software Coroventis Coroflow (*Coroventis Abbott, Uppsala, Sweden)*.

- FFR is defined as the ratio of maximal coronary blood flow in a diseased artery to maximal coronary blood flow in the same artery without stenosis. FFR is a surrogate marker of inducible myocardial ischemia caused by epicardial coronary stenosis.

- CFR is the ratio of hyperemic to baseline flow and is a marker of the integrity of both epicardial and microvascular coronary circulation. Therefore, CFR represents the microvascular status when there is no significant epicardial disease.

- IMR is the minimum achievable coronary microcirculatory resistance and a more specific marker of the coronary microcirculation. It is calculated as the ratio of distal coronary pressure to coronary flow at hyperemia and presented in units (mmHg.s).

The physiological study assessing IMR, CFR and FFR will be repeated again one year after HT.

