***Changes in EMB protocol based on coronary microvascular resistance***

- Each center will specify the number of annual biopsies performed based on IMR values obtained between the first two months after HT.

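### The primary biopsy count starts at transplant, before IMR is known, and the protocol gives two conflicting windows for the IMR that sets the biopsy number

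*Protocol*

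**What the plan says.** **The count.** Protocol Section 3.4 sets the primary outcome as to "evaluate IMR values and number of EMB performed in the first year after HT". Section 2.2 and the Endpoints section of the embedded protocol use the same window, and its Summary table lists "Number of biopsies performed in the first year". No section starts the count at the IMR study, leaves out earlier biopsies or adjusts for them.

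**When IMR is known.** The Procedure section states: "Patients included will undergo a coronary angiography between the first and third month after HT".

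**How IMR acts on the count.** Section 3.4 continues: "If the IMR is less than 15, the number of biopsies could be reduced or kept the same". At 15 or above, biopsies follow the centre's usual protocol. The Hypothesis section reads the same way: "Low IMR values in the first three months could reduce the number of protocol EMB".

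**Usual number.** Section 2.1 says of biopsy that "it is usually repeated up to 5 times during the first year", with variation between centres. No schedule by month is given.

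**A related exclusion.** Section 3.2 excludes "Patients with acute cellular rejection before intracoronary physiological assessment". This removes some patients. It does not remove the pre-IMR biopsies of those who remain.

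**A second window.** The section on changes in the EMB protocol has each centre specify its number of annual biopsies "based on IMR values obtained between the first two months after HT".

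**The concern.** The hypothesis concerns what happens to biopsies once IMR is known. An outcome that counts from transplant mixes biopsies that IMR could influence with biopsies already done. The second kind carries no information on IMR guidance, but it enlarges the denominator of any relative reduction and adds variance. The IMR groups are not randomised and biopsy protocols differ by centre, so pre-IMR counts may differ between the groups for reasons unrelated to guidance. Such a difference would pass straight into the primary contrast.

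The conflict over the IMR window is a separate defect in the same outcome. It leaves unclear which patients have an IMR that may set their biopsy number, and which measurement is the baseline for the IMR change.

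**Working it through.** **1. The plan's own figure.** The only planning number is 100 patients, and it rests on centre volume. Reading the 10 to 15 transplants per centre as yearly, 8 × 10 = 80 to 8 × 15 = 120 per year, or 160 to 240 over the two-year recruitment period. That is compatible with 100. No effect size, SD, power or split between IMR groups is stated, so there is no power figure to reproduce.

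**2. Share of biopsies before IMR.** The documents do not give it. Assuming an even spread over 12 months, share = month of IMR / 12:
- IMR at month 1: 1/12 = 8.3%
- IMR at month 2: 2/12 = 16.7%
- IMR at month 3: 3/12 = 25%

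**3. Effect on a relative reduction.** Observed reduction = true reduction × (1 − share). For a true 50% cut after IMR:
- month 1: 0.5 × 0.917 = 45.8%
- month 3: 0.5 × 0.75 = 37.5%

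A front-loaded schedule raises the share. With 5 biopsies in the year, of which *k* precede IMR (*k* assumed), observed reduction = 0.5 × (5 − *k*)/5:

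| *k* before IMR | Reduction in year total | Reduction after IMR |
| --- | --- | --- |
| 1 | 40% | 50% |
| 2 | 30% | 50% |
| 3 | 20% | 50% |
| 4 | 10% | 50% |

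**4. Effect on an absolute difference.** Year-total difference = post-IMR difference + difference in pre-IMR means. If the pre-IMR means are equal, the expected difference is unchanged and only the variance grows: SD_total = √(SD_post² + SD_pre²), taking the two counts as independent. If they are unequal, the year-total difference is biased by exactly that inequality.

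Illustration, with all inputs assumed: a difference of 0.5 biopsies, SD_post = 1.0, 50 patients per IMR group, two-sided 0.05. Power = Φ(0.5 / (SD × √(2/50)) − 1.96).

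| SD_pre | SD used | Power | n per group for 80% |
| --- | --- | --- | --- |
| none (post-IMR count) | 1.00 | 70.5% | 63 |
| 0.5 | 1.12 | 60.9% | 79 |
| 1.0 | 1.41 | 42.4% | 126 |

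**5. Which denominator for a post-IMR count.** Dividing by days at risk assumes a constant biopsy rate. Take 5 biopsies in the year, 3 of them evenly spaced in months 0 to 3, and no IMR effect. A patient studied at month 1 has 4 left in 11 months, 4/11 = 0.36 per month. A patient studied at month 3 has 2 left in 9 months, 2/9 = 0.22 per month. The ratio is 0.61 from the date of the study alone. Dividing by the number the centre schedules for the same period gives 4/4 and 2/2, a ratio of 1.

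**6. The IMR window, section by section.**
- Up to three months, or month 1 to 3: Section 3.4 (primary outcome and the IMR-variation outcome), the Summary table's primary endpoint, Hypothesis, Procedure.
- Up to two months, or month 1 to 2: Section 2.2 and Endpoints (IMR variation), the Summary table's secondary endpoints, the Study Variables schedule, and the section on changes in the EMB protocol.

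A study done in month 3 is on protocol under Procedure. It is outside the Study Variables column and outside the section that ties the biopsy number to IMR. The IMR-variation endpoint has two definitions, and the Summary table carries both windows.

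**The case against.** The whole-year count has a real defence. It matches the hypothesis as written, measures the patient's total biopsy burden over equal follow-up, and uses the same reference as the centre protocols and the section on annual biopsies. With equal pre-IMR counts, the absolute difference between groups is not shrunk at all. The protocol states no relative reduction or power that the dilution would invalidate. A naive post-IMR rate per day can also create a spurious difference, as step 5 shows, which the whole-year count avoids.

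Much of this stands. The loss is confined to relative and standardised effects, to precision, and to bias where pre-IMR counts differ. The whole-year total deserves reporting. The step 5 problem rules out days at risk as the denominator, but not a comparison with the centre's schedule for the same period. The defence does not answer the main point: biopsies done before IMR cannot show whether IMR guidance changed anything, and in a non-randomised comparison nothing ensures that they balance. It does not bear on the conflicting window, which should be settled whatever is decided about the count.

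**Conclusion.** The point holds. The protocol itself fixes a counting window that opens one to three months before the IMR result can act, and it gives two incompatible windows for that IMR. The size of the dilution cannot be derived from the documents. Under an assumed even spread, a 50% cut appears as 46% to 37.5%; a front-loaded schedule would make it smaller. The power figures are illustrations on assumed SDs. The window conflict rests on no assumption.

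Three stronger readings are tempting and not supported:
- **That the dilution amounts to losing half the sample.** A reader might infer this from the last power row (126 against 63). It needs SD_pre equal to SD_post, and the documents give neither. With an even spread and variance proportional to the count, the standardised effect falls only by √(1 − share), a factor of 0.96 to 0.87.
- **That the survival analyses run on a transplant-based clock and so include a rejection-free period by design.** Section 3.12.1 and the Statistical analysis section name Kaplan-Meier and Cox methods but fix no time origin. An analysis plan may set it.
- **That the date of the IMR study confounds the comparison.** This would need the date to be associated with IMR group, and no section indicates that it is.

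**What to change.** **Counting window.** Make the primary comparison of IMR groups on biopsies performed after the IMR study up to month 12, or to death or re-transplantation if earlier. Relate the count to the number that the centre's own protocol schedules for that same period, for example with log scheduled biopsies as the offset in a count model. Do not use log days. Keep the whole-year total and the pre-IMR count, by IMR group, as descriptive results.

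**IMR window.** Reconcile Sections 2.2 and 3.4 and the embedded Summary, Study Variables, Endpoints, Hypothesis, Procedure and EMB-protocol sections to one definition. Which window applies is for the investigators to decide.

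**Cost.** No extra patients or procedures, and no change to clinical management from the counting rule. The study must record the IMR date, the biopsy dates and each centre's biopsy schedule. The real downside is a change to the primary outcome of a registered trial that is already recruiting. It needs a documented amendment, reported in the registry as Section 4.2 provides, before the analysis at 100 patients.

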**- Secondary outcomes:**

-IMR variation between first three months after HT and one year: Comparison between the values of index of microvascular resistance (IMR) measured by bolus thermodilution technique between the first and 3rd month after HT and one year in the invasive physiological study. IMR may be expressed as mmHg·s.

-Acute cellular rejection: A ≥2R degree according to the 2010 ISHLT system. Two or more focal infiltration points associated with myocyte injury in EMB. Diffuse infiltration with multi-focal myocyte injury with/without oedema, hemorrhage or vasculitis.Time frame: One year.

-Cardiac allograft vasculopathy: Accelerated fibroproliferative process characterized by diffuse, concentric and longitudinal thickening of the intima of the vascular tree of the graft, affecting everything from the major epicardial arteries to the coronary microvasculature.Time frame: 5 years.

-Cardiovascular mortality:Caused by cardiovascular disease or unknown death. Time frame: 5 years.

-Heart failure: Diastolic or systolic heart failure after heart transplant. Time Frame: Five years.

-Inmunosupressive therapy: Changes in any of the inmunosuppresive agents pre-established in each center heart transplant protocol. Time Frame: Five years

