**STUDY VARIABLES**

| **Event** | **Screening** | **1-2 month(s)**  **post-transplantation** | **12 months**  **post-transplantation** | **Annual**  **for 5 years** |
| --- | --- | --- | --- | --- |
| **Criteria** **for**  **inclusion/exclusion** | X |  |  |  |
| **Informed**  **consent** | X |  |  |  |
| **Laboratory test** | X | X |  |  |
| **Echocardiogram** | X | X | X |  |
| **Medication** | X | X | X |  |
| **Functional invasive coronary test** |  | X | X |  |
| **Events during**  **follow-up** |  |  | X | X |

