**STUDY DESIGN**

**ENDPOINTS**

*The main objective* of the study is to evaluate IMR values and number of EMB performed in the first year after HT.

S*econdary endpoints* are:

- Analyze the relationship between ACR and IMR.
- Analyze the relationship between CV mortality and IMR.
- Analyze the relationship between CAV and IMR.
- Analyze the relationship between the variation IMR value in the first two months and one year, and cardiovascular events.
- Analyze the relationship between the combined endpoint of ACR, heart failure, re-transplantation, CV mortality and IMR.
- Assessment of immunosuppressive therapy after IMR results.

All endpoints will be evaluated at 1 year, and annually thereafter for up to 5 years.

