***Definition of events***

- **Acute cellular rejection (ACR**): A ≥2R degree according to the 2010 ISHLT system. Two or more focal infiltration points associated with myocyte injury in EMB. Diffuse infiltration with multi-focal myocyte injury with/without oedema, hemorrhage or vasculitis (2).
- **Cardiovascular mortality:** Caused by cardiovascular disease or unknown death.
- **Cardiac allograft vasculopathy:** Accelerated fibroproliferative process characterized by diffuse, concentric and longitudinal thickening of the intima of the vascular tree of the graft, affecting everything from the major epicardial arteries to the coronary microvasculature (2).
- **Combined endpoint:** ACR, heart failure, re-transplantation and cardiovascular mortality.
- **Cardiac catheterization complications:** any complication (major or minor) related to the performance of EMB, coronary angiography and functional study.

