***Statistical analysis***

The characteristics of the study population will be summarized through standard descriptive statistics. Continuous variables will be expressed as mean (± standard deviation) or median [interquartile range (IQR)], as appropriate. Discrete variables will be presented as absolute numbers and percentages. For the comparison of means, the Student's t test for independent measures or the non-parametric Mann-Whitney U test (in the case of dichotomous qualitative variables) and the ANOVA or non-parametric Kruskal test will be used as a hypothesis test. Wallis (in the case of non-dichotomous qualitative variables). For the bivariate analysis of the qualitative variables, the Chi-square test or Fisher's exact test will be used. Events will be compared between groups by using Kaplan-Meier curves. Cox regression analysis will be performed to adjust for confounding factors and to evaluate independent predictors of clinical events. A two-tailed p-value of 0.05 will be considered statistically significant. All statistical analyses will be performed by SPSS software.

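### CAV is a five-year event outcome, but no coronary study is scheduled after month 12 and the protocol does not say how CAV is found in years 2 to 5

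*Protocol*

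**What the plan says.** - **Outcome and time frame.** Section 3.4, secondary outcomes, ends its CAV entry with "coronary microvasculature.Time frame: 5 years".
- **Definition.** Under Definition of events, CAV is structural: "Accelerated fibroproliferative process characterized by diffuse, concentric and longitudinal thickening of the intima of the vascular tree of the graft". No imaging method, grade or reading rule is attached.
- **Coronary studies.** The Procedure section states: "Patients included will undergo a coronary angiography between the first and third month after HT". It then adds: "The physiological study assessing IMR, CFR and FFR will be repeated again one year after HT". Nothing later is planned.
- **Schedule.** In the Study Variables table, the row "Functional invasive coronary test" is marked at 1-2 months and at 12 months. Its annual cell is empty. The annual column holds only a mark for follow-up events, and echocardiography also stops at month 12.
- **Promise of evaluation.** The Endpoints section says: "All endpoints will be evaluated at 1 year, and annually thereafter for up to 5 years". The summary table gives follow-up as "1 year and annually for five years".
- **Conflicting text.** Section 3.10.2 and the Data and follow-up section place the assessment of clinical events at one month and one year, with no later time.
- **Analysis.** Section 3.12.1 and the Statistical analysis section say: "Events will be compared between groups by using Kaplan-Meier curves". Cox regression follows for adjustment.

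**The concern.** Thickening of the coronary intima cannot be ruled out at an annual contact unless someone has examined the coronaries. Standard Kaplan-Meier and Cox calculations keep a patient with no recorded CAV at risk and event-free until the last contact, and they date CAV at whichever study happened to find it. If the last contact is at year 5 and the last coronary study was at month 12, four years of unobserved time enter the denominator as CAV-free.

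Two things are at stake. The first is the level: recorded five-year CAV may be too low. The second is the comparison: the objective is the relationship between CAV and IMR, the trial summary gives masking as none, and management after the IMR result is discretionary. If later imaging happened to depend on IMR, the recorded CAV rates could differ by IMR group even with equal true rates. Adjusting for confounders in a Cox model would not remove that.

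**Working it through.** The protocol gives no CAV rate, effect size or power, so there is no figure of its own to reproduce. The check compares sections, and an illustration of size follows.

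**1. Sections side by side**

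| Item | Months 1-3 | Month 12 | Years 2-5 |
|---|---|---|---|
| Coronary study (Procedure, Study Variables) | yes | yes | none scheduled |
| Event recording (Study Variables) | no | yes | yes, annually |
| Event assessment (3.10.2, Data and follow-up) | month 1 | yes | not mentioned |
| Evaluation of all endpoints (Endpoints) | not mentioned | yes | yes, annually; no method for CAV |

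The rows do not agree on years 2-5, and none of them says how CAV would be ascertained then.

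**2. Share of the window without a protocol coronary study**

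(60 − 12) / 60 = 48 / 60 = 80%.

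**3. Possible understatement (assumptions, not protocol figures)**

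Assume a constant CAV hazard h, so F(t) = 1 − exp(−ht). Assume also that the month-12 study finds all CAV present by then, that a share p of patients is re-imaged by year 5 with all their CAV found, and that nobody else's later CAV is found. Then:

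recorded risk = F(1) + p × [F(5) − F(1)]

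| h per year | F(1) | F(5) | p = 0 | p = 0.5 | p = 0.75 | p = 1 |
|---|---|---|---|---|---|---|
| 0.04 | 3.9% | 18.1% | 3.9% | 11.0% | 14.6% | 18.1% |
| 0.07 | 6.8% | 29.5% | 6.8% | 18.1% | 23.8% | 29.5% |
| 0.10 | 9.5% | 39.3% | 9.5% | 24.4% | 31.9% | 39.3% |
| Understatement | | | 76-78% | 38-39% | 19-20% | 0% |

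Example: for h = 0.04 and p = 0.5, 0.0392 + 0.5 × (0.1813 − 0.0392) = 0.110, and 1 − 0.110 / 0.181 = 39%. The relative loss hardly depends on h. It is driven by p, which the protocol does not give.

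**4. Possible distortion of the CAV-by-IMR comparison (hypothetical)**

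Keep the true hazard equal in both IMR groups and let only the re-imaged share differ. The apparent hazard ratio is approximately ln(1 − R_high) / ln(1 − R_low), where R is the recorded risk.

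- 70% against 50% re-imaged: 1.28 to 1.29 across the three hazards.
- 80% against 40% re-imaged: 1.64 to 1.68.
- Equal shares: 1.00.

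No section supports any particular split.

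**5. Timing**

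The only stated analysis trigger is 100 patients completing the first year. That analysis ends where the scheduled coronary study falls, so it is little affected. The problem concerns the later follow-up analyses.

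**The case against.** The strongest reply is that the schedule row covers the pressure-wire study, and that an empty cell there does not mean no coronary imaging. The table has no row for angiography, and none for biopsy although biopsy count is a primary outcome, so it does not list everything done to these patients. The early angiography is described as routine in most centres. The methods text calls the study observational, so later imaging may follow centre practice. All this stands. A reader might infer that nobody looks after month 12, but the documents are silent on that and do not show it.

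Second, the protocol does not write that un-imaged patients count as CAV-free. That is what the named methods do by default, and a statistical analysis plan, not seen here, could set another censoring rule. This too stands. But such a plan cannot recover imaging dates that were never collected, and the protocol does not call for collecting them. The disagreement among the protocol's own sections also remains.

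Third, a reader might infer that high-IMR patients will be imaged more often, so that a CAV-by-IMR association would be an artefact. The documents do not support this. The Biopsies and immunosuppressive therapy section ties IMR only to biopsy number and immunosuppression. Lack of masking and discretionary management make differential imaging possible, no more.

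Fourth, the illustration assumes that the month-12 study ascertains CAV. No section says CAV is read or graded then. This is a fair limit on the figures and on any 12-month CAV result.

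**Conclusion.** The point holds in a limited form. The protocol sets a five-year structural coronary outcome and names time-to-event methods for it. It schedules no coronary study in the last 80% of the window, and it contradicts itself on whether events are assessed after year 1. If centres do not image routinely, five-year CAV could be understated under the default calculation. If they all do, there may be no loss.

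The documents establish the 48 months without a scheduled study and the unreconciled sections. They do not establish that five-year CAV will be understated, by 39% or any other amount, or that the IMR comparison is biased. Those sizes rest wholly on the assumed hazards, re-imaged shares and perfect detection when imaged. Nor do they require the five-year outcome to give way to a 12-month one, which would answer a different question.

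This is a secondary outcome and the one-year analysis is little touched, so the point should be corrected but does not threaten the primary result. It is best done now, because imaging dates are harder to recover later.

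**What to change.** 1. Reconcile section 3.4, section 3.10.2, the Study Variables table, Endpoints, Procedure, and Data and follow-up, so that they agree on whether and how CAV is followed after month 12. State what counts as a positive and a negative study for CAV; that criterion is for the investigators.
2. At each annual contact, record the date and result of any coronary imaging already done under centre routine.
3. Keep the five-year outcome. Analyse CAV as interval-censored between the last negative and the first positive study, and end CAV follow-up at the last coronary study instead of the last contact.
4. Report the frequency of coronary imaging by IMR group, so that readers can judge whether ascertainment differed.
5. Give CAV at the 12-month study as an additional result, as a proportion of the patients studied.

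The cost is two data fields per annual contact and a change to the analysis text. There will be fewer person-years and wider intervals for years 2 to 5. No procedure is added for any patient.
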